### 8.3 PROCEDURES FOR DISCONTINUATION/WITHDRAWAL

- **Documentation:** All discontinuations or withdrawals will be documented, including the reason and date.
- **Data Management:** Data collected up to the point of withdrawal will be retained and used in analyses unless the participant requests otherwise.
- **Continuous Communication:** Study staff will maintain regular communication to address concerns and potentially prevent withdrawal.

The principles of respect, safety, and voluntary participation will guide all decisions related to discontinuation and withdrawal. Participants will receive appropriate counselling and support throughout this process.

## 9 STUDY ASSESSMENTS AND PROCEDURES

This section outlines the comprehensive approach for standardizing data collection, measurement modalities, and assessment procedures for the trial. The aim is to ensure consistency, reliability, and validity across all sites and participants.

### 9.1 ENDPOINT AND OTHER NON-SAFETY ASSESSMENTS

#### A. Primary Endpoint:

- **Health-Related Quality of Life:**

- **Tool:** EQ-5D-5L Index (EuroQol Group, 1990)
- **Assessment:** Administered at 0, 6, and 12 months. Investigator administered.

**B. Secondary Endpoints:**

i. **Frailty Index:**

- a. **Tool:** Cumulative Deficit Frailty Index (Rockwood et al., 2005)
- b. **Details of the index:** The study will employ a deficit-based frailty index (FI) to assess frailty status, following the cumulative deficit model (Ghosh et al., 2023). The FI will be constructed using 40 health-related variables covering multiple domains, including chronic diseases, functional limitations, cognitive impairments, and self-perceived health status. Each variable will be coded as 0 (deficit absent), 1 (deficit present), or assigned an intermediate value (e.g., 0.5) for partial deficits. The FI score for each participant will be calculated by dividing the total number of deficits present by the total number of variables assessed, resulting in a score ranging from 0 to 1. Based on this score, participants will be categorized as robust ( $FI \leq 0.15$ ), prefrail ( $FI > 0.15$  to  $\leq 0.24$ ), or frail ( $FI > 0.25$ ). This method provides a comprehensive and standardized approach to measuring frailty by accounting for the accumulation of health deficits across multiple domains.
- c. **Assessment Schedule:** Assessed at baseline, 6, and 12 months.

ii. **ADL/IADL:**

- a. **Tool:** Lawton and Brody Instrumental Activities of Daily Living Scale (Lawton & Brody, 1969)
- b. **Assessment Schedule:** Conducted at baseline, 6, and 12 months.

iii. **Healthcare Utilization:**

- a. **Tool:** Custom questionnaire capturing healthcare visits and hospital admissions.
  - b. **Data Collection:** Monthly via participant health diaries and healthcare records.
- iv. **Healthcare Expenditure:**
  - a. **Assessment:** Monthly data collection from participant reports and receipt submissions.
- v. **Medication Adherence:**
  - a. **Tool:** Medication Adherence Reporting Scale (MARS) (Thompson et al., 2000)
  - b. **Frequency:** Assessed at 0, 6, and 12 months.
- vi. **Patient Satisfaction:**
  - a. **Tool:** Patient Satisfaction Questionnaire (Greenfield & Attkisson, 1989)
  - b. **Frequency:** Evaluated at 6, and 12 months.
- vii. **Mortality Rates:**
  - a. **Data Collection:** Continuous monitoring throughout the study period using health records and family reports.

## 9.2 SAFETY ASSESSMENTS

- **Adverse Events:**
  - **Definition:** Any undesirable experience associated with the use of the intervention.
  - **Assessment Frequency:** Continuous monitoring with mandatory reporting within 24 hours of occurrence.

- **Severity Classification:** Mild, Moderate, Severe based on impact on daily activities.
- **Serious Adverse Events:**
  - **Definition:** Events resulting in death, hospitalization, disability, or jeopardizing participant health.
  - **Reporting:** Immediate notification to Principal Investigator and ethics board, with documentation filed timely.
- **Vital Signs and Routine Checks:**
  - **Parameters:** Blood pressure, heart rate, weight, and BMI.
  - **Frequency:** Monthly during contact sessions.
- **Lab Tests:** (also as outcomes as described above in section 3.2)
  - **Assessment Schedule:** 0, 6, and 12 months.
  - **Tests Included:** (detailed as endpoints in section 3.2)
    - **Biochemical Metrics:** Blood glucose, lipid profile, liver function tests, kidney function tests.
    - **Hematological Metrics:** Complete blood count, hemoglobin levels.
    - **Micronutrient Profiles:** Levels of Vitamin D, iron, and calcium.
    - **Hormonal Profiles:** Thyroid function tests and other relevant hormone levels.

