## 10 ADVERSE EVENTS AND SERIOUS ADVERSE EVENTS

### 10.1 DEFINITION OF ADVERSE EVENTS (AEs)

An adverse event (AE) is any undesirable medical occurrence in a trial participant that may present during the trial, whether related to the intervention or not. This includes any new symptoms or worsening of pre-existing conditions.

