### 10.2 DEFINITION OF SERIOUS ADVERSE EVENTS (SAEs)

A serious adverse event (SAE) is an AE that results in any of the following outcomes:

- Death
- Life-threatening condition
- Hospitalization or prolongation of existing hospitalization
- Persistent or significant disability/incapacity
- Any other medically important condition

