#### 10.5 ADVERSE EVENT REPORTING

- AEs will be documented in the participant's case report form within 24 hours of awareness.

- UDetails to include: description, onset date, severity, relationship to intervention, and outcome.
- Relationship with AE and intervention: This will be decided by a panel of clinicians and advisory board experts along with investigators to classify each AE as described above in 8.3.3.
- Regular Regular review (quarterly) to ensure timely reporting and management.

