#### 12.4.4 SAFETY ANALYSES:

Frequency and severity comparisons across groups in terms of AE and SAE reported and other details from documentation in safety reports.

---

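### Protocol sections 9.2 and 10.1 give conflicting definitions of an adverse event; if 9.2 governed ascertainment, the between-group comparison of non-serious events would be biased

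*Protocol*

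**What the plan says.** Section 9.2 of the protocol, within the chapter on assessments and procedures, defines an AE as "Any undesirable experience associated with the use of the intervention". It asks for continuous monitoring with "mandatory reporting within 24 hours of occurrence". Its SAE definition is "Events resulting in death, hospitalization, disability, or jeopardizing participant health".

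Section 10.1 defines an AE as "any undesirable medical occurrence in a trial participant that may present during the trial, whether related to the intervention or not". Section 10.2 defines an SAE as an AE with one of several listed outcomes, among them "Life-threatening condition". Section 10.3 grades relationship to the intervention on five levels, the lowest of which is for events that are not related. Section 10.5 says that "AEs will be documented in the participant's case report form within 24 hours of awareness", lists relationship among the details to be entered, and gives the classification to a panel of clinicians, advisory board experts and investigators.

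The planned safety analysis in 12.4.4 is "Frequency and severity comparisons across groups in terms of AE and SAE reported", plus details from the safety reports. The interim analysis in 12.4.7 also reviews the incidence and severity of AEs and SAEs. Neither section says which definition applies.

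**The concern.** Under 10.1, relationship to the intervention is judged after an event has been recorded. Under 9.2, it decides whether there is an AE at all. A participant on routine care does not receive the package, so an experience associated with its use can hardly arise there. In the Multi-FrAME arm, the number of AEs would depend on how readily someone links an event to the package.

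Many of the risks listed in section 2.3.1 are usually non-serious: gastrointestinal symptoms, strains and sprains, fatigue, dizziness. In frail people aged 60 and over with several chronic conditions, such complaints also occur without any intervention, and they can be interpreted only against a control-arm count collected in the same way. If that count is almost empty by definition, neither the final comparison nor the interim review can separate an effect of the package from background. No later analysis can recover events that were never written down.

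**Working it through.** There is no figure to reproduce. The protocol states no AE rate and no rate at which events would be attributed to the package. The check is a comparison of the text.

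1. **Entry condition for an AE.** Section 9.2 requires association with the intervention. Section 10.1 requires only that the occurrence be undesirable, medical and during the trial. An unrelated event is an AE under 10.1 and not under 9.2. The two cannot both hold, and no order of precedence is stated.

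2. **Which definition the rest of the protocol assumes.** The not-related category in 10.3 would be empty if 9.2 governed. Section 10.5 records relationship as an attribute of each AE, and the list of forms in section 15 has relation to intervention as a variable on the AE/SAE form. All three fit 10.1. Section 9.2 is the exception, but section 9 opens by saying that it standardises data collection and assessment across all sites and participants, so staff could reasonably work from it.

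3. **Effect on AE counts, by arm, if 9.2 were applied.**
   - Routine care: almost no non-serious AEs. The count is not strictly zero, because section 12.4.8 foresees that some controls may take up intervention components.
   - Multi-FrAME: only events that someone has already linked to the package. Section 6.2 has the package delivered by health centre professionals helped by study investigators. The blinding in 4.2, 6.4 and 12.4.1 covers outcome evaluators and data analysts, not those delivering care. That unblinded staff would make this first judgement is an inference; the protocol does not say who would.
   - Direction: the control count is pushed close to zero and the intervention count is reduced only in part. The difference therefore leans towards an apparent excess with the package, while total events in both arms are understated.

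4. **Effect on SAE counts.** The 9.2 SAE definition contains no link to the intervention, so SAEs remain countable in both arms under 9.2 read on its own. One route to trouble remains: 10.2 makes an SAE a kind of AE, so a reader who combined the 9.2 AE definition with 10.2 would carry the restriction over.

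5. **Effect if 10.1 were applied.** AEs and SAEs are countable in both arms on the same terms, and the definition gives no reason to doubt the comparison in 12.4.4.

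6. **Reporting clock.** Section 9.2 counts 24 hours from occurrence and 10.5 counts 24 hours from awareness. An event first mentioned at a monthly contact session more than a day after it happened meets the second rule and cannot meet the first.

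**The case against.** The strongest reply is that 9.2 is a summary bullet and that the chapter devoted to AEs uses the broad definition throughout. The analysis in 12.4.4 draws on reported events and safety reports, which is the section 10 route. Sites are to be trained in identifying AEs and SAEs (section 1.2), and an operating manual, not shown here, may settle the matter. This has weight. A reader might infer that the planned comparison is invalid as it stands, and the documents do not support that: it is compromised only where 9.2 is actually used for ascertainment.

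A reader might also infer that control participants can have no adverse events of any kind, or that harms such as cardiac events or hypercalcaemia could not be judged against background. That goes too far as well. SAEs under 9.2 are counted in either arm, admissions and deaths are collected as secondary endpoints (9.1), and calcium is measured at 0, 6 and 12 months with no restriction by arm. The exposure is confined to non-serious AEs.

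Two side issues are smaller than they look. The shorter SAE wording in 9.2 includes jeopardy to health, which plausibly covers life-threatening events, and prolonged hospitalisation is arguably within hospitalisation. The two clocks may describe different acts (reporting and form completion), and the hotline in 10.4 allows participants to report at any time.

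What survives is the contradiction itself. Two labelled definitions give different event sets, and the analysis sections choose neither.

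**Conclusion.** The two AE definitions conflict and must be reconciled. The consequence is conditional: if the 9.2 wording were used to ascertain events, non-serious AEs under routine care would be missed almost entirely, Multi-FrAME counts would depend on prior attribution, and the between-group AE comparison in 12.4.4 and the interim safety review would be biased. Under 10.1 this problem does not arise. SAEs as defined in 9.2 are unaffected, and so are the primary endpoint and its analysis.

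The direction follows from the wording. The size does not, since it would need a background event rate and an attribution rate that the protocol does not give. The conclusion assumes that no training material or manual already tells sites to use 10.1. Even if one does, the protocol text remains wrong as written.

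**What to change.** - Delete the AE and SAE definitions in 9.2 and refer to 10.1 and 10.2 as the only definitions, applied identically in both arms. Name them in 12.4.4 and 12.4.7 as the basis of the counts.
- State that every event is recorded first, and that its relationship to the intervention is then assigned by the panel described in 10.5. That section points to 8.3.3 for the categories, a section the protocol does not contain; they are in 10.3, and the reference should be corrected in the same edit.
- Reconcile the occurrence-based clock in 9.2 with the awareness-based clock in 10.5, so that one starting point applies.
- Align the AE/SAE form instructions and site training. If enrolment has begun, establish which definition sites have been using before anyone relies on the counts.

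The cost is protocol wording and form instructions, with no added visits. More unrelated non-serious events will have to be recorded in both arms, and the panel will have more of them to classify.

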### 9.3 DATA COLLECTION AND MANAGEMENT

- **Health Diaries:**
  - Participants will maintain daily logs.
  - Collected monthly for centralized data entry and analysis.

- **Standard Operating Procedures (SOPs):**

- Detailed SOPs will guide assessors in administering tools and conducting interviews to ensure consistency.

- **Training of Field Staff:**

- All staff and assessors will undergo training sessions using detailed manuals, including mock assessments and role plays to ensure precision and reliability in data collection.
- Refresher trainings will be held at 6 month interval and in case of staff turnover.
- The Manual of Operating Procedures is prepared and will be used for training.

## 10 ADVERSE EVENTS AND SERIOUS ADVERSE EVENTS

### 10.1 DEFINITION OF ADVERSE EVENTS (AEs)

An adverse event (AE) is any undesirable medical occurrence in a trial participant that may present during the trial, whether related to the intervention or not. This includes any new symptoms or worsening of pre-existing conditions.

### 10.2 DEFINITION OF SERIOUS ADVERSE EVENTS (SAEs)

A serious adverse event (SAE) is an AE that results in any of the following outcomes:

- Death
- Life-threatening condition
- Hospitalization or prolongation of existing hospitalization
- Persistent or significant disability/incapacity
- Any other medically important condition

### 10.3 CLASSIFICATION OF AN ADVERSE EVENT

- **Severity of Event:**
  - Mild: Temporary and easily tolerated.
  - Moderate: Causes discomfort and interrupts normal activities.
  - Severe: Incapacitating and significantly impacts daily life.
- **Relationship to Study Intervention/Experimental Manipulation:**
  - Not related: Clearly due to other causes.
  - Unlikely related: Temporal relationship but unlikely to be associated.
  - Possibly related: Temporal relationship with a possible causal link.
  - Probably related: Likely caused by the intervention.
  - Definitely related: A direct result of the intervention.

#### 10.4 TIME PERIOD AND FREQUENCY FOR EVENT ASSESSMENT AND FOLLOW-UP

- AEs will be assessed continuously throughout the trial.
- Participants will be followed up telephonically through a hotline number for the duration of the trial. This will be bi-directional, with participants having the ability to report AE anytime they face.
- Participants will be monitored monthly during contact sessions.
- Any AE reported will be followed up until resolution or stabilization.

#### 10.5 ADVERSE EVENT REPORTING

- AEs will be documented in the participant's case report form within 24 hours of awareness.

- UDetails to include: description, onset date, severity, relationship to intervention, and outcome.
- Relationship with AE and intervention: This will be decided by a panel of clinicians and advisory board experts along with investigators to classify each AE as described above in 8.3.3.
- Regular Regular review (quarterly) to ensure timely reporting and management.

## 10.6 SERIOUS ADVERSE EVENT REPORTING

- SAEs will be reported immediately (within 24 hours) to the Principal Investigator and ethics committee, along with the managing clinician.
- A detailed SAE report will include all relevant medical information and follow-up actions.

## 10.7 REPORTING EVENTS TO PARTICIPANTS

- Participants will be informed of any AEs or SAEs related to their participation.
- Communication will be clear and compassionate, with explanations of implications and any necessary actions.
- All other lab investigations and reports will be communicated to the participants through routine follow-up channels of the trial.

## 10.8 EVENTS OF SPECIAL INTEREST

- Events of special interest include those that might not meet SAE criteria but are significant due to the nature of the intervention (e.g., unexpected physiological changes).
- These will be monitored closely and reported similarly to SAEs to facilitate understanding of intervention-related risks.

## 11 UNANTICIPATED PROBLEMS

### 11.1 DEFINITION OF UNANTICIPATED PROBLEMS

Unanticipated problems refer to incidents, experiences, or outcomes that are unexpected in nature, severity, or frequency given the research setting and relevant subject population. These problems may affect the safety, rights, or well-being of participants or others involved in the trial.

### 11.2 UNANTICIPATED PROBLEMS REPORTING

- **Immediate Reporting:** All unanticipated problems will be reported to the Principal Investigator and ethics committee within 24 hours of identification.
- **Documentation:** A thorough incident report will be created detailing the nature of the problem, circumstances of occurrence, and any immediate corrective actions taken.
- **Review and Action:** The ethics committee will periodically review the report to determine further actions, including protocol amendments or participant safety measures.

### 11.3 REPORTING UNANTICIPATED PROBLEMS TO PARTICIPANTS

- **Timely Communication:** Participants affected by unanticipated problems will be informed promptly. The communication will provide a clear explanation of the problem, potential impacts, and any changes to their involvement or care.
- **Support and Guidance:** Participants will receive appropriate support and counselling to address concerns and ensure their continued well-being and informed participation.

## 12 STATISTICAL CONSIDERATIONS

### 12.1 STATISTICAL HYPOTHESES

- **Null Hypothesis (H0):** The Multi-FrAME intervention package has no effect on frailty progression, functional ability, health-related quality of life, healthcare utilization, or life satisfaction compared to routine care.

- **Alternative Hypothesis (HA):** The Multi-FrAME intervention package significantly improves frailty progression, functional ability, health-related quality of life, healthcare utilization, or life satisfaction compared to routine care.

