## 1 PROTOCOL SUMMARY

### 1.1 SYNOPSIS

**Title:** Effectiveness and Implementation of a Primary Healthcare Intervention for Screening and Management of Multimorbidity and Frailty among Urban Older Adults: The Multi-FrAME Study

**Design:** Phase 3 cluster randomized, parallel arm, observer-blinded trial.

**Objective:** To assess the effectiveness of the Multi-FrAME intervention package in improving health outcomes for older adults with multimorbidity and frailty.

**Setting:** Urban Primary Healthcare Centres (PHCs) in Bhubaneswar, India.

**Participants:** Older adults (aged 60+) with multimorbidity and frailty (Frailty Index  $\geq 25$ ), without dementia, and not bedridden.

**Intervention:** The Multi-FrAME package, which includes medical management, nutritional support, physiotherapy, physical activity, and psychosocial counselling.

**Comparator:** Standard routine care.

**Primary Outcome:** Improvement in health-related quality of life, measured by EQ-5D-5L index scores.

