### 3 OBJECTIVES AND ENDPOINTS

The primary healthcare intervention package (Multi-FrAME) is expected to improve health outcomes for older adults with multimorbidity and frailty, including a reduction in frailty progression and enhanced functional ability. This will assess the following outcomes.

| Objectives                                                                                      | Endpoints                                                   | Justification For Endpoints                                                       | Putative Mechanisms Of Action                                   |
|-------------------------------------------------------------------------------------------------|-------------------------------------------------------------|-----------------------------------------------------------------------------------|-----------------------------------------------------------------|
| 3.1 PRIMARY OBJECTIVES                                                                          |                                                             |                                                                                   |                                                                 |
| Assess the effectiveness of the Multi-FrAME package in improving health-related quality of life | Change in EQ-5D-5L index scores at 0, 6, and 12 months      | EQ-5D-5L is validated for use in India and measures multiple dimensions of health | Comprehensive care improves physical, mental, and social health |
| 3.2 SECONDARY OBJECTIVES                                                                        |                                                             |                                                                                   |                                                                 |
| Evaluate improvement in frailty                                                                 | Change in frailty index scores (deficit accumulation model) | Reliable measure for frailty changes                                              | Nutritional support and physical activity reduce frailty        |
| Assess improvement in ADL/IADL                                                                  | Change in ADL/IADL scores using Lawton IADL Scale           | Validated measure for functional status                                           | Improved physical and cognitive functioning                     |

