## 12.2 SAMPLE SIZE DETERMINATION

- **Assumptions:**

- Mean Quality of life utility scores of control group = 0.87 [SD=0.17] (Jyani et al., 2023)
- Effect size: Based on anticipated (clinically meaningful) improvement of 10% in HRQoL scores ([name] et al., 2025)
- Power: 90%
- Significance level: 0.05
- Intra-cluster correlation: 0.24 ([name] et al., 2023)
- Attrition rate: 25%

- **Calculation Methodology:** The following steps were used for the calculation of sample size

1. Effect size calculation

Effect size is the standardized mean difference between the control and intervention groups: calculated using the following formula,

$$Effect\ Size\ (Cohen's\ d) = \frac{Mean\ difference\ (Improvement)}{SD}$$

2. Sample size for two sample t-tests

The formula to calculate the sample size for a two-sample t-test is based on the following

$$n = \frac{(Z_{1-\alpha/2} + Z_{1-\beta})^2}{d^2} * \frac{2(SD)^2}{Effect\ size}$$

Where:

- $Z_{1-\alpha/2}$  is the critical value for a two-tailed test at the significance level  $\alpha$ .
- $Z_{1-\beta}$  is the critical value corresponding to the desired power  $(1-\beta)$ .
- $d$  is the effect size.
- $SD$  is the standard deviation

The `pwr.t.test()` function in R is used to perform this calculation, which outputs the required sample size for each arm of the trial assuming a simple t-test.

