#### 12.4.2 ANALYSIS OF THE PRIMARY ENDPOINT(S)

- **Outcome:** Health-related quality of life measured by EQ-5D-5L.
- **Method:** The primary outcome of this study is health-related quality of life, assessed using the EQ-5D-5L scale. The EQ-5D-5L instrument measures quality of life across five domains

(mobility, self-care, usual activities, pain/discomfort, and anxiety/depression), with each domain scored on five levels of severity. An overall utility score for quality of life will be calculated by mapping these responses to a single index value, facilitating comparison across participants. This index value is a continuous interval measure that allows for nuanced assessment of changes in health status. Primary outcome measures will be compared between the intervention and control groups using appropriate statistical tests based on the nature of the outcome variables (e.g., t-tests, chi-square tests, or non-parametric tests) to assess differences in outcomes. We will use adjusted Odds ratios arrived at using mixed effect models to calculate effect sizes and corresponding confidence intervals to quantify the magnitude of intervention effects.

---

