#### 12.4.3 ANALYSIS OF THE SECONDARY ENDPOINT(S)

- **Outcomes:** Frailty progression, ADL/IADL scores, healthcare utilization, costs, patient satisfaction, medication adherence, mortality, along with all the laboratory measurements.
- **Method:** Each secondary outcome will be clearly defined and analyzed to evaluate the broader impacts of the intervention on participants' health and well-being. Frailty progression will be assessed through a frailty score as a continuous measure. Functional limitations will include work-limiting conditions, mobility, Activities of Daily Living (ADL), and Instrumental Activities of Daily Living (IADL), scored on an ordinal scale, using categorical measures (e.g., "able" vs. "unable"). Health care utilization will be measured by tracking healthcare events (e.g., visits, hospitalizations) in a binary or categorical format, while health care expenditure will be recorded as a continuous variable, capturing both mean and median expenditures. Medical adherence will be represented as a percentage, indicating the proportion of prescribed medications participants adhered to. Statistical comparisons of these secondary outcomes between the intervention and control groups will employ appropriate tests for each outcome variable type to assess differences. Mixed-effect models will calculate adjusted odds ratios to determine effect sizes, with corresponding confidence intervals to quantify the intervention's impact.

---

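### Section 12.1 states one hypothesis over five outcomes joined by *or*, which conflicts with the single EQ-5D-5L primary outcome; no primary visit is named.

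*Protocol*

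**What the plan says.** Section 12.1 gives one null and one alternative over the same five outcomes. Under the null the package "has no effect on frailty progression, functional ability, health-related quality of life, healthcare utilization, or life satisfaction compared to routine care"; under the alternative it "significantly improves frailty progression, functional ability, health-related quality of life, healthcare utilization, or life satisfaction compared to routine care". Neither gives the EQ-5D-5L any priority.

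The rest of the protocol has a clear hierarchy:

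- **Primary.** The synopsis gives "Improvement in health-related quality of life, measured by EQ-5D-5L index scores". Section 12.4.2 states: "The primary outcome of this study is health-related quality of life, assessed using the EQ-5D-5L scale". The schema and section 9.1 agree.
- **Secondary.** Section 12.4.3 lists "Frailty progression, ADL/IADL scores, healthcare utilization, costs, patient satisfaction, medication adherence, mortality, along with all the laboratory measurements". The synopsis and sections 3.2 and 9.1 also place frailty, ADL/IADL and utilization here.
- **Sample size.** Section 12.2 uses a quality-of-life mean, SD and improvement only, with "Significance level: 0.05" and a critical value that "is the critical value for a two-tailed test at the significance level".
- **Time.** The objectives table in section 3 defines the primary endpoint as "Change in EQ-5D-5L index scores at 0, 6, and 12 months". Sections 9.1 and 12.4.2 do not choose a visit.

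**The concern.** The null in 12.1 denies an effect on any of the five outcomes, so its logical opposite is an effect on at least one. Read literally, a significant gain in frailty index or utilization would satisfy the alternative even if the EQ-5D-5L showed nothing. That does not fit a trial sized on quality of life alone, with frailty and utilization ranked as secondary.

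Nor does the list work as a summary of the endpoints. It omits expenditure, medication adherence, patient satisfaction and mortality, all of them listed secondary endpoints. It includes life satisfaction, which has no endpoint, instrument or row in the schedule of activities. The nearest endpoint is patient satisfaction with care, which is a different construct.

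The open visit is a second, smaller gap. Change at month 0 is zero by definition, so two candidate results remain, at 6 and 12 months, and the protocol does not say which one is primary.

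At stake is what the trial may claim. If these points are settled only after results by arm are known, any choice will look post hoc.

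**Working it through.** **1. The five outcomes in 12.1 against the rest of the protocol**

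| Outcome in 12.1 | Status elsewhere |
|---|---|
| Frailty progression | Secondary (3.2, 9.1, 12.4.3) |
| Functional ability | Secondary, as ADL/IADL (3.2, 9.1, 12.4.3) |
| Quality of life | Primary (1.1, 1.2, 3.1, 9.1, 12.4.2); basis of 12.2 |
| Healthcare utilization | Secondary (3.2, 9.1, 12.4.3) |
| Life satisfaction | No endpoint or instrument; otherwise only in background and benefit text (2.1, 2.3.2) |

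Four of the five can be tested, and one of those four is primary.

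**2. Error rate if any one outcome counted as success**

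The protocol states no family-wise error rate, so there is no figure to reproduce. Inputs: alpha 0.05, two-sided (12.2); k = 4 measurable outcomes, or k = 5 as listed; a common correlation rho between test statistics, all scored so that higher is better. The protocol gives no correlation, so rho is an assumption.

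Independent tests:

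- Either direction: 1 − 0.95^4 = 0.185 and 1 − 0.95^5 = 0.226.
- Benefit only, at 0.025 per test: 1 − 0.975^4 = 0.096 and 1 − 0.975^5 = 0.119.

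Correlated tests, with c = 1.96, integrating over a shared standard normal x:

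- Either direction: 1 − ∫ φ(x) [Φ((c − √rho·x)/√(1 − rho)) − Φ((−c − √rho·x)/√(1 − rho))]^k dx.
- Benefit only: the same without the second Φ term.

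| rho | k = 4, either direction | k = 4, benefit | k = 5, either direction | k = 5, benefit |
|---|---|---|---|---|
| 0 | 18.5% | 9.6% | 22.6% | 11.9% |
| 0.3 | 17.4% | 8.7% | 20.9% | 10.5% |
| 0.5 | 15.6% | 7.8% | 18.3% | 9.2% |
| 0.7 | 13.0% | 6.5% | 14.8% | 7.4% |
| 0.8 | 11.4% | 5.7% | 12.7% | 6.4% |

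A single test gives 5% and 2.5%. The alternative is worded as improvement, so the benefit columns are the ones that answer to a false claim of success.

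**3. EQ-5D-5L alone, free choice of 6 or 12 months**

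Independent: 1 − 0.95^2 = 9.8% in either direction and 1 − 0.975^2 = 4.9% for benefit. At rho = 0.7 the same integrals give about 8.4% and 4.2%.

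**4. Effect of the fix on sample size**

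Reading the 10% improvement in 12.2 as 0.10 × 0.87 = 0.087 gives d = 0.087/0.17 = 0.512. The usual two-sample normal approximation at 90% power then gives:

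- One test at 0.05: n = 2(1.960 + 1.282)²/0.512² ≈ 80.2, so 81 per arm before clustering and attrition.
- Five outcomes under Bonferroni, 0.01 each: n = 2(2.576 + 1.282)²/0.512² ≈ 113.7, so 114 per arm for the EQ-5D-5L test.

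A single primary test keeps the alpha that 12.2 already uses, so 81 stands.

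**The case against.** The strongest reply is that 12.1 is a loosely drafted study-level hypothesis, not a decision rule. It contains no rejection rule, no alpha per outcome and no criterion for success. The 0.05 appears only in 12.2, in a calculation on quality of life. The hierarchy is consistent everywhere else, and 12.4.2 does analyse the outcome on which the trial was sized. All of this stands. It limits the finding to a conflict between 12.1 and the other sections.

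A reader might infer more than the protocol supports:

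- **That the trial carries roughly a 20% chance of a false claim.** That figure counts rejections in either direction, includes harm, counts an outcome the trial never measures, and assumes low to moderate correlation. It also needs any one outcome to count as success, which no section states. Higher correlation is plausible: the frailty index in 9.1 includes functional limitations and self-perceived health, and the EQ-5D-5L covers mobility, self-care and usual activities.
- **That the time points contradict a single primary outcome.** They do not. The 0, 6 and 12 month list reads as an assessment schedule. The schema places the endline at 12 months, and 12.4.7 times the interim analysis by 12-month completion. Both point to 12 months, but neither makes it primary.
- **That there is no error control at all.** Handling of multiple secondary outcomes is commonly left to the SAP, which is not at hand. The protocol's own multiplicity statements cover only subgroup and exploratory analyses (12.4.8, 12.4.10).

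What remains is that the only formal hypothesis in the protocol does not match its primary outcome. Rewording 12.1 is the direct way to settle that.

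**Conclusion.** The point holds as a conflict of wording plus an under-specified primary visit. Section 12.1 gives five outcomes equal standing where the rest of the protocol has one primary outcome, and one of the five has no endpoint.

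The size is conditional. If any one of the four measurable outcomes counted as success at two-sided 0.05, false benefit would be about 8-10% and rejection in either direction about 16-19%. For all five as listed, the ranges are 9-12% and 18-23%. These assume correlations of 0 to 0.5. At 0.8 the five-outcome figures fall to 6.4% and 12.7%.

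This should be fixed. It is not a fatal flaw: the hierarchy in the other sections is sound, and the remedy is wording only.

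**What to change.** - **12.1:** restate the null and alternative as one two-sided 0.05 hypothesis on the between-arm difference in EQ-5D-5L index at one named visit. Twelve months fits the endline visit and the interim timing.
- **3.1 and 12.4.2:** name that visit as primary and make 6 months secondary.
- **Other outcomes:** list frailty, function and utilization as secondary hypotheses that cannot by themselves make the trial positive.
- **Life satisfaction:** delete it, or replace it with patient satisfaction, which has an instrument and visits.

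Data collection and sample size do not change. The sponsor gives up the option of claiming success on a secondary outcome. The change should be made before anyone sees outcome results by arm, including those from the planned interim analysis.
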